## Abstract

**Background:**

Hypertension affects 29% of the adult U.S. population and is a leading cause of heart disease, stroke, and kidney failure. Despite numerous effective treatments, only 53% of people with hypertension are at goal blood pressure. The chronic care model suggests that blood pressure control can be achieved by improving how patients and physicians address patient self-care.

**Methods and design:**

This paper describes the protocol of a nested 2 × 2 randomized controlled trial to test the separate and combined effects on systolic blood pressure of a behavioral intervention for patients and a quality improvement-type intervention for physicians. Primary care practices were randomly assigned to the physician intervention or to the physician control condition. Physician randomization occurred at the clinic level. The physician intervention included training and performance monitoring. The training comprised 2 internet-based modules detailing both the JNC-7 hypertension guidelines and lifestyle modifications for hypertension. Performance data were collected for 18 months, and feedback was provided to physicians every 3 months. Patient participants in both intervention and control clinics were individually randomized to the patient intervention or to usual care. The patient intervention consisted of a 6-month behavioral intervention conducted by trained interventionists in 20 group sessions, followed by 12 monthly phone contacts by community health advisors. Follow-up measurements were performed at 6 and 18 months. The primary outcome was the mean change in systolic blood pressure at 6 months. Secondary outcomes were diastolic blood pressure and the proportion of patients with adequate blood pressure control at 6 and 18 months.

**Discussion:**

Overall, 8 practices (4 per treatment group), 32 physicians (4 per practice; 16 per treatment group), and 574 patients (289 control and 285 intervention) were enrolled. Baseline characteristics of patients and providers and the challenges faced during study implementation are presented. The HIP interventions may improve blood pressure control and lower cardiovascular disease risk in a primary care practice setting by addressing key components of the chronic care model. The study design allows an assessment of the effectiveness and cost of physician and patient interventions separately, so that health care organizations can make informed decisions about implementation of 1 or both interventions in the context of local resources.

**Trial registration:**

ClinicalTrials.gov identifier NCT00201136

## Background

Approximately 50 million adult Americans have hypertension [1], which is the most prevalent risk factor for cardiovascular and kidney disease [2] and accounts for approximately 35% of atherosclerotic cardiovascular disease (CVD) [3]. Fortunately, the treatment of hypertension reduces associated risks: lowering blood pressure (BP) by a variety of strategies reduces the risk of stroke by approximately 35%, congestive heart failure by 42%, and coronary heart disease by 28% [4-7]. Therefore, an important key to reducing the burden of hypertension-related CVD is to increase the proportion of patients who achieve optimal BP control. To promote this goal, the Joint National Committee on Prevention, Evaluation, Detection, and Treatment of High Blood Pressure (JNC) has established guidelines that have been widely disseminated to practitioners through the National Institutes of Health High Blood Pressure Education Program and other organizations [8].

The latest JNC guidelines (JNC-7), published in 2003, classify BP into stages and provide recommendations for treatment and follow-up. The recommended goal for patients with uncomplicated hypertension is an average systolic BP of less than 140 mm Hg and a diastolic BP of less than 90 mm Hg. For patients with certain comorbid conditions that increase risk (i.e., diabetes mellitus and chronic kidney disease), the goal BP is less than 130/80 mm Hg [8].

Treatments for high blood pressure are classified as lifestyle modification or medication. The guidelines direct physicians to prescribe lifestyle modification to all patients with BP that is above the optimal category (> 120/80 mm Hg). The recommendations for lifestyle modification are evidence-based and include adoption of a healthy dietary pattern such as the Dietary Approaches to Stop Hypertension (DASH) diet [9], losing weight if overweight, reducing sodium intake, increasing physical activity, and limiting alcohol intake [8]. Each of these behavioral interventions has been shown to lower BP and contribute to hypertension control. For medication therapy, the guidelines indicate when and whom to treat and also provide advice on choice of drug, when and how to adjust doses, and how to minimize non-adherence to therapy. The explicit intent of the guidelines is to assist physicians in achieving goal BP in the majority of their patients.

Two behaviors that could improve BP control are physicians' adherence to JNC-7 guidelines and patients' adherence to lifestyle recommendations and medication regimens. Several similarities exist between behavioral models that attempt to explain why physicians do or do not follow guidelines for preventive care [10,11] and those that attempt to explain why patients do or do not adopt healthy lifestyle behaviors [12,13]. For the physician, awareness (knowledge), motivation, and confidence (self-efficacy) all influence adherence to guidelines. For instance, physicians who do not know about or do not feel motivated to follow the JNC guidelines are not likely to prescribe them, nor are physicians who have the knowledge and motivation but lack confidence to follow the guidelines. Non-behavioral factors can also influence physicians' actions. These include external or systems-level factors such as time constraints, resources, and systems to prompt or remind physicians of the guidelines [10,11,14].

Similarly, behavioral factors may also influence patients' adherence to lifestyle recommendations and medications [12,13]. Patients who are unaware that they need to change their behavior or who are not motivated will not change. In addition, external factors including food availability and environmental structures may affect how patients adhere to a healthy lifestyle. The Hypertension Improvement Project (HIP) behavioral interventions were designed to target the same psychosocial mediators and systems factors for both physicians and patients, presented graphically in Figure 1.

**Figure 1 F1:**
[figure not shown]
**Psychosocial mediators and systems factors that influence physician and patient adherence to JNC-7 guidelines**. MD = physician.

Strategies for implementing recommended practice to improve clinical outcomes include dissemination of printed educational materials (e.g., clinical practice guidelines), physician and patient training, feedback to physicians, dissemination of information linked to performance (e.g., audit and feedback, reminder systems), clinical performance measures (CPMs), and simple clinical bedside tools. Although randomized trials of these strategies are rare, there is evidence that such tools can change medical provider behavior and improve clinical outcomes [15-17]. A major challenge is the integration of practice improvement strategies into the flow of clinical care; to accomplish this, health researchers and providers have borrowed techniques of Continuous Quality Improvement (CQI). It is the application of a CQI approach–applying tools shown to be effective–that forms the foundation for the HIP physician intervention.

The patient also plays a critical role in hypertension care. As noted above, the JNC guidelines include lifestyle modification for all patients with hypertension. Programs that result in successful lifestyle behavior change are generally based on Social Cognitive Theory [12] and techniques of behavioral self-management [18]. They are typically constructed using the Transtheoretical Model [13,19] and motivational enhancement approaches [20,21]. These approaches emphasize the importance of the individual's ability to regulate behavior by setting goals, developing specific behavior change plans, monitoring progress towards the goals, and attaining skills necessary to reach the goals. Self-efficacy (i.e., one's confidence in performing a given behavior) and outcome expectations (i.e., one's belief that changing behavior leads to a favorable outcome) are critical mediators of behavior change [12,22]. An example of this approach can be found in the PREMIER trial of lifestyle interventions for blood pressure control–a multi-center trial sponsored by the National Heart, Lung, and Blood Institute that tested the effects on BP of 2 multi-component lifestyle interventions, relative to an advice-only control condition [23]. The PREMIER study demonstrated that a 6-month intensive behavioral intervention leads to healthy lifestyle changes, significant reductions in BP, and improved control of hypertension.

As is true for most chronic illnesses, hypertension management requires extensive efforts from physicians and patients alike, with support from the health care system. It was hypothesized that a quality improvement approach would maximize physician adherence to treatment guidelines, and a behavioral intervention would improve patient adherence to lifestyle recommendations. Both approaches may lead to significant improvements in BP control with consequent reductions in CVD risk. The HIP study offers a unique and innovative opportunity to test this hypothesis by determining, in a randomized controlled trial, the separate and combined effect on BP of a physician intervention and a patient intervention. The study design provides for an assessment of the effectiveness and cost of implementing the physician and patient interventions separately, thereby allowing health care organizations to make informed decisions about implementation of 1 or both interventions in the context of local resources. As participant enrollment concludes and data cleaning and analysis begin, this paper describes the protocol of the HIP trial and discusses the lessons learned thus far from designing and implementing the study, including issues encountered and subsequent changes to the study design.

## Methods and design

### Overview

The HIP study was a nested 2 × 2 randomized controlled trial of a physician intervention, a patient intervention, and both combined (Figure 2). All study procedures were approved by the Duke Institutional Review Board. Recruitment was conducted in waves: i.e., 2 practices were initiated every 6 months to allow adequate time for study personnel to train providers and recruit participants. Each group of practices was considered a cohort (e.g., the first 2 practices recruited are considered Cohort 1). Nesting occurred at the level of the practice and the level of the physician. Primary care practices were randomly assigned to the physician (MD) intervention or to the MD control condition. All participating MDs within a given practice had the same randomization assignment. The MD intervention consisted of training and performance monitoring. Performance data were collected for 18 months, and feedback was provided to physicians every 3 months within that timeframe.

**Figure 2 F2:**
[figure not shown]
**Design of the HIP study**. MD = physician.

Within the practices, patient participants were individually randomized to the patient intervention or to usual care. The patient intervention occurred shortly after initiation of the physician intervention and consisted of a 6-month group-based behavioral intervention conducted by trained interventionists, followed by brief monthly phone counseling for 12 months from a community health advisor (CHA). Follow-up measurements were performed at 6 and 18 months following randomization.

### Enrollment and randomization of MDs

To avoid contamination among physicians in the same practice, randomization occurred at the level of the practice. Four matched pairs of primary care practices were randomly assigned to physician intervention or control. Practices were matched according to specialty (internal medicine or family practice) and participant mix (percent of participants with Medicaid or Medicare without supplemental insurance). Within each practice, all physicians were invited to participate, with a goal of enrolling 4 physicians at each clinic. All physicians at a given clinic were assigned to the same intervention.

### Enrollment and randomization of patients

After enrolling clinics and physicians, participants were then recruited from the patients of the enrolled physicians. Ten to 15 patients cared for by each participating MD were enrolled and randomized to the behavioral intervention or usual care.

Billing codes were used to identify hypertensive patients. Each participating physician reviewed the list and removed names of patients considered unsuitable candidates for study participation. Recruitment letters were mailed on practice letterhead with the physician's name on the signature line. Patients were asked to call the research coordinator within 10 working days to decline participation in the study. After the 10 days, a member from the study staff called unresponsive patients to assess their willingness and eligibility to participate (Table 1).

**Table 1 T1:** HIP eligibility criteria

**Inclusion criteria**	• Receiving primary care from a randomized physician
	• Diagnosis of hypertension: Average SBP ≥ 140 mm Hg and/or DBP ≥ 90 mm Hg on at least 2 clinic visits in the past 12 months or taking antihypertensive medication
	• Age 25 years or older at the time of the initial screening visit
	• Willing and able to participate fully in all aspects of the intervention
**Exclusion criteria**	• Cardiovascular event within the past 6 months (if more remote history, eligible with MD approval)
	• Chronic kidney disease (estimated GFR < 60 ml/min)
	• Planning to leave the area prior to the anticipated end of participation
	• Pregnant, breast feeding, or planning pregnancy prior to the end of participation
	• Current participation in another clinical trial
	• Investigator discretion for safety or adherence reasons
	• Household member of another HIP participant or of an HIP staff member

DBP = diastolic blood pressure; GFR = glomerular filtration rate; HIP = Hypertension Improvement Project; MD = physician; SBP = systolic blood pressure.

At the first screening visit, the consent form was reviewed and signed, height, weight and BP were measured, and body mass index (BMI) was calculated. A self-administered medical history questionnaire was used to establish the final set of eligibility criteria. At a second screening visit, questionnaires and interviews established the patient's commitment and ability to participate, and a fasting blood specimen, 24-hour urine collection, and a second BP measurement were obtained. Participant baseline characteristics are shown in Table 2.

**Table 2 T2:** Baseline patient characteristics (N = 574)

**Characteristic**	**%***
N	574

Age, mean years (SD)	60.5 (11.4)

Female sex	61

Completed high school	93

Adequate income (self-reported)	85

African-American race	37

Medical history	

Taking BP medications	95

Ever smoked	48

Physical activity (accelerometry), mean minutes/week (SD)	34 (106)

Diabetes	30

Hyperlipidemia	48

* Unless otherwise indicated.

BP = blood pressure; SD = standard deviation.

After eligibility was established, randomization occurred using a computer-generated algorithm, stratified by cohort and by clinic. Participants were randomized in varying block sizes to ensure comparable numbers of participants in each assignment over time. Each participant learned of his/her treatment assignment from a HIP staff member who was not involved in collecting study measurements. Intervention staff members then instructed participants on the details of their assigned intervention.

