The CHAs served as familiar, non-authoritative resources for study participants, strengthening communication between the research group and the participants and providing additional social support. The intent is that the CHAs will have sufficient knowledge and skills to serve as ongoing resources in their communities and to help sustain the effects of the project after it is completed.

The outcomes were measured at the level of the patient, who was exposed to neither intervention, MD intervention alone, patient intervention alone, or both interventions. Overall, 8 practices (4 per treatment group), 32 physicians (4 per practice; 16 per treatment group), and 574 patients (289 control and 285 intervention) were enrolled (Figure 2).

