### Physician measurements

Measurements specific to the physician intervention are described above. All physicians, regardless of treatment assignment, were asked to complete a baseline questionnaire concerning their demographics, education, and training–variables that are potential mediators of the effect of the physician intervention on BP control (Table 4). In addition, at entry, 6 months, and 18 months, all physicians were asked to complete a questionnaire in which they reported their practice patterns and habits. For example, providers reported the average amount of time spent discussing hypertension and lifestyle changes with patients, in addition to addressing barriers to, confidence in, and patient adherence to lifestyle modification counseling.

**Table 4 T4:** Baseline physician characteristics (N = 32)

**Characteristic**	**%***
Age, mean years (SD)	47.9 (9.9)

Female sex	34

African-American race	16

Family medicine specialty	53

Internal medicine specialty	47

Years since MD degree, mean (SD)	20.7 (10.0)

Patients with HTN	28.9

Very familiar with JNC guidelines	31

* Unless otherwise indicated.

HTN = hypertension; JNC = Joint National Committee on Prevention, Evaluation, Detection, and Treatment of High Blood Pressure; SD = standard deviation.

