### Sample size and statistical power

The power calculations assumed that the impact of accounting for covariates such as baseline blood pressure (which increases statistical power) and the impact of the clustering inherent to this design (which decreases statistical power) would approximately offset and, thus, that power calculations from the 1-way analysis of variance would apply. If so, having approximately 340 patients complete the study would yield approximately 80% power to detect main effects, although the power to detect an interaction between the physician intervention and patient intervention would be smaller. After accounting for expected drop-outs, the minimum sample size for the primary analysis was set at 400.

Preliminary planning also considered 2 other factors, both of which supported an increase in the sample size above 400, if feasible. First, it was anticipated that the study would analyze various secondary outcome variables, some of which might have effect sizes that were less than 0.3. Second, so that the results could be as generalizable as possible, the study strove to include as many clinics as possible. The design originally intended to include 5 sets of clinics, a number which was also suggested by the fact that the most conservative statistical analysis of the impact of the physician intervention–namely, a sign test that simply counts which clinic out of each pair had the better outcome–would be statistically significant if the physician intervention outperformed the controls at each pair of clinics.

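### The stated 10 to 15 patients per physician cannot yield the 574 enrolled, and the 80% power figure should not cover the practice-randomized physician effect

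*Protocol article*

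**What the plan says.** Under *Enrollment and randomization of patients* the article reports, as something done, that "Ten to 15 patients cared for by each participating MD were enrolled and randomized to the behavioral intervention or usual care". The same section says that "participants were then recruited from the patients of the enrolled physicians", so patients had no other source.

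The totals, from 8 practices, stand in the Abstract and at the end of *Active intervention: structure and content*: "32 physicians (4 per practice; 16 per treatment group), and 574 patients (289 control and 285 intervention) were enrolled". The table captions repeat both counts: "Baseline patient characteristics (N = 574") and "Baseline physician characteristics (N = 32").

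*Enrollment and randomization of MDs* makes the practice the unit randomized to the physician intervention, with four matched pairs and a goal of four physicians per clinic. *Sample size and statistical power* says that five sets of clinics were first intended.

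That section uses neither a number of patients per physician nor an intracluster correlation (ICC). It assumes that the gain from covariates and "the impact of the clustering inherent to this design (which decreases statistical power) would approximately offset". On that basis it claims about 80% power for the main effects with roughly 340 completers, and sets a minimum enrolment of 400.

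**The concern.** The average number of patients per physician lies above the stated maximum. Whatever the distribution, some physicians must have contributed more than 15.

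The sentence is the article's only statement of patients per physician. Multiplied by four physicians, it also implies a practice size. A reader working out a design effect from it would use clusters that are too small at both levels.

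Cluster size matters most for the physician intervention, because it was randomized by practice and its main effect is one of the three primary hypotheses in the *Analysis plan*. The single figure of about 80% covers this effect and the individually randomized patient effect alike, although clustering by practice acts on them very differently.

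**Working it through.** **Inputs from the article.** 8 practices, 32 physicians, 574 patients (289 + 285), 10 to 15 patients per physician, 5 sets of clinics originally planned, about 340 completers, minimum 400, and about 80% power.

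**Assumptions, not in the article.** Two-sided alpha 0.05; effect size 0.3 for the primary outcome (the article names 0.3 only in passing); the ICC values; baseline R-squared 0.25; 15% drop-out, as implied by 340/400 = 0.85.

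**1. The count.**
- 32 × 10 = 320 and 32 × 15 = 480. The upper end is 574 − 480 = 94 short.
- 574/32 = 17.94 per physician, which is 20% above 15 (17.94/15 = 1.196).
- 574/8 = 71.75 per practice, against 4 × 10 = 40 to 4 × 15 = 60 implied by the sentence.
- 574/15 = 38.3, so at least 39 physicians would be needed.
- Original plan: 5 pairs × 2 practices × 4 physicians = 40 physicians; 40 × 10 = 400 and 40 × 15 = 600. This range contains both 574 and the minimum of 400.

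**2. The plan's own power figure.** For two equal groups, power ≈ Φ(d√N/2 − 1.96). With d = 0.3 and N = 340, this is Φ(2.766 − 1.960) = Φ(0.806) = 0.79. The stated figure of about 80% reproduces, and 340/0.85 = 400. No cluster size is used, so the miscount changes neither number.

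**3. What the wrong range does to a design effect.** Design effect = 1 + (m − 1) × ICC.

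| Level | ICC | As stated | As enrolled |
|---|---|---|---|
| Physician (m = 10 to 15; 17.94) | 0.01 | 1.09 to 1.14 | 1.17 |
| Physician | 0.05 | 1.45 to 1.70 | 1.85 |
| Practice (m = 40 to 60; 71.75) | 0.01 | 1.39 to 1.59 | 1.71 |
| Practice | 0.05 | 2.95 to 3.95 | 4.54 |

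**4. Power for the physician effect.**
- Completers: 574 × 0.85 = 488, or m = 488/8 = 61 per practice.
- Variance factor V = (1 − 0.25) × (1 + 60 × ICC); standard error = √(4V/488) in SD units; noncentrality = 0.3/standard error.
- Two-sided t test on 8 − 2 = 6 degrees of freedom (critical value 2.447), power from the noncentral t distribution.

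| Practice ICC | V | Standard error | Noncentrality | Power |
|---|---|---|---|---|
| 0.01 | 1.20 | 0.0992 | 3.03 | 71% |
| 0.02 | 1.65 | 0.1163 | 2.58 | 58% |
| 0.05 | 3.00 | 0.1568 | 1.91 | 36% |

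This sketch applies R-squared to the whole variance and ignores the pair matching. The planned adjustment for the four cohorts would use 3 of the 6 degrees of freedom if they are counted at practice level, but might also remove some variance between practices.

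**The case against.** The strongest reply is that nothing in the plan depends on the 10 to 15. The totals are prominent and consistent, and from them anyone can derive 17.9 and 71.75. The power section never uses the range, and it records a past planning assumption for a trial whose enrolment is complete. The reduction from five sets of clinics to four cohorts is openly explained. An ICC range is also detail that an article may leave to the full protocol.

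Most of this stands. It makes the count a reporting error and not a design fault. It does not remove the contradiction:
- Ten to 15 per physician in each arm would give 640 to 960, which also excludes 574.
- Physician turnover does not explain it, since departing physicians' patients went to other participating physicians and the count stays at 32.
- Reading the range as a target conflicts with the sentence's own wording, which reports enrolment.

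On power, omitting the ICC from an article is not the complaint. The complaint is that the article states one figure for two effects randomized at different levels.

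A reader might infer two stronger conclusions, and neither is supported:
- **That patients beyond the plan add almost nothing for the physician effect.** Compare 340 completers in 10 practices with 488 in 8. Effective sizes are 128 and 122 at ICC 0.05 (340/2.65; 488/4.00), 205 and 222 at 0.02 (340/1.66; 488/2.20), and 256 and 305 at 0.01 (340/1.33; 488/1.60). The last is a 19% gain. The article gives no ICC, so the claim cannot be made.
- **That having fewer practices raises the design effect.** At a fixed cluster size the formula does not contain the number of practices. Losing a pair costs clusters and degrees of freedom, which is a separate loss.

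**Conclusion.** The contradiction is certain and rests only on the article's own numbers: at most 480 patients under the stated range against 574 enrolled. That the range is left over from the 40-physician plan is likely but inferred. The error alters neither 340 nor 400, and it does not put the enrolment total in doubt.

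The claim of about 80% power is fair as a planning figure for the individually randomized patient effect. It should not be read as covering the physician effect. There, with 8 practices, illustrative power is about 71%, 58% and 36% at a practice ICC of 0.01, 0.02 and 0.05. Those values depend on the assumed effect size, drop-out, R-squared and degrees of freedom. They show the direction and rough size of the gap and are not estimates for this trial.

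**What to change.** 1. In *Enrollment and randomization of patients*, label 10 to 15 as the original target, or replace it with the actual number per physician (mean 17.9, with the observed range) and per practice (mean 71.75, with the observed range).
2. In *Sample size and statistical power*, limit the 80% statement to the patient effect. State power for the physician effect separately, using 8 practices, about 72 patients enrolled per practice, practice-level degrees of freedom and a stated ICC range.

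The cost is one corrected number and a less favourable power statement for the physician effect. No change to design, enrolment or data collection is needed.
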